## Abstract

**Background:**

Intensive combined lifestyle interventions are the recommended treatment for severely obese children and adolescents, but there is a lack of studies and their cost-effectiveness. The objective of this study is to compare the cost-effectiveness of two intensive one-year inpatient treatments and usual care for severely obese children and adolescents.

**Methods/Design:**

Participants are 40 children aged 8-13 and 40 adolescents aged 13-18 with severe obesity (SDS-BMI ≥ 3.0 or SDS-BMI ≥ 2.3 with obesity related co-morbidity). They will be randomized into two groups that will receive a comprehensive treatment program of 12 months that focuses on nutrition, physical activity and behavior change of the participant and their parents. The two programs are the same in total duration (12 months), but differ in inpatient treatment duration. Group A will participate in a 6 month intensive inpatient treatment program during weekdays, followed by six monthly return visits of 2 days. Group B will participate in a 2 month intensive inpatient treatment program during weekdays, followed by biweekly return visits of 2 days during the next four months, followed by six monthly return visits of 2 days. Several different health care professionals are involved, such as pediatricians, dieticians, psychologists, social workers, nurses and physiotherapists. Results will also be compared to a control group that receives usual care. The primary outcome is SDS-BMI. Secondary outcomes include quality of life using the EQ-5D and cardiovascular risk factors. Data will be collected at baseline and after 6, 12 and 24 months. An economic evaluation will be conducted alongside this study. Healthcare consumption will be based on actual resource use, using prospective data collection during 2 years through cost diaries. Quality Adjusted Life Years (QALYs) will be calculated using the EQ-5D.

**Discussion:**

This study will provide useful information on the effectiveness and cost-effectiveness of inpatient treatment in severely obese children and adolescents. Valuable information on long term effects, after 2 years, is also included.

**Trial registration:**

Netherlands Trial Register (NTR): NTR1678

## Background

In the Netherlands the prevalence of obesity in children and adolescents has increased during the last decades [1-3]. Generally, when an increase in prevalence is observed, there is a skewed distribution to the right instead of a normal distribution, which means that a disproportional large increase in the prevalence of severe obesity is observed [4]. The prevalence of obesity in children aged 4-15 years has increased from 0.2 to 2.6% in boys and from 0.5 to 3.3% in girls in the period 1980-2003 [3]. These trends are worrisome because obesity in children is associated with an increased risk of several chronic diseases such as diabetes type 2 and cardiovascular diseases and musculoskeletal, respiratory and psychosocial problems [5,6]. Obesity also tracks from childhood into adulthood and is predictive for significant health consequences in later life independent of adult BMI [7-9]. Besides having an adverse impact on healthy life years and quality of life, childhood obesity also has a substantial impact on health care utilization and results in a heavy financial burden for society [10,11]. Although many programs for the treatment of obesity exist, results have not been very promising, especially regarding their long term effectiveness. Nevertheless, a recent systematic review of inpatient programs for children showed greater reductions in the percentage overweight participants at post treatment and at follow-up compared with results from a recent meta-analysis of out-patient treatments [12]. Studies evaluating the effectiveness of treatment programs (with or without an inpatient period) aimed at children with severe obesity are relatively rare [12,13]. However, it has been suggested that ambulatory programs for severely obese children and adolescents are insufficiently effective and that there is a need for experienced, specialized pediatric obesity centers for intensive treatment by professionals with expertise in pediatric and adolescent medicine [14,15]. Spear et al. describe the need for comprehensive treatments that should be provided by multidisciplinary obesity care teams, including for example social workers, psychologists, dieticians, and exercise specialists [16]. The ideal approach in such comprehensive treatments would include dietary modification, an increase in physical activity, a reduction in sedentary activity and behavior modification [17,18]. A promising alternative for ambulatory care is inpatient treatment in specialized centers as mentioned above [12]. Heideheuvel (part of Merem Treatment Centers) is the only specialized clinic in the Netherlands offering an intensive combined lifestyle inpatient intervention, focusing on nutrition, physical activity and behavior change of the participants and their parents. This lifestyle intervention has a duration of 12 months, with a 6 month inpatient period and is designed for severely obese children and adolescents between 8 and 18 years. However such a lengthy inpatient treatment program involves high costs and a considerable burden for both the child and the family. Therefore, a new intensive combined lifestyle intervention also with a duration of 12 months, but with a shorter inpatient period (2 months) was developed at Heideheuvel with the aim of being equally effective but less costly and disturbing for family life.

The objective of this study is to compare the cost-effectiveness of these two intensive one-year inpatient treatments to each other and to usual care for severely obese children and adolescents.

## Methods/Design

### Design

This study is designed as a randomized controlled clinical trial with three study arms. The cost-effectiveness of two intensive one-year treatments that vary in inpatient period length and usual care for severely obese children and adolescents will be evaluated. There is a one year follow-up after treatment. Participants who meet the inclusion criteria and consent to participate in the study will be randomized to one of the three study arms (described under 'interventions'). Because of the nature of the treatments evaluated in this study, parents and participants as well as professionals at Heideheuvel and in the usual care condition cannot be blinded to the type of intervention. A table of random numbers is used to randomize participants. At the beginning of the first year 40 (13-18 years) participants are randomized into: group A (10), group B (10) or group C (20). The participants in group C will be randomized into group A (10) or B (10) after one year of receiving usual care. This process is repeated for another 40 participants (8-13 years) after 6 months. At the end of the fourth year all 80 participants (40 in each inpatient treatment group) will have completed the program and 1 year of follow up (Figure 1). Data collection started in August 2009 and will continue until July 2013. The Medical Ethics committee (METc) of VU University Medical Centre approved the study design, protocol and informed consent procedures.

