### Participants

The study population consists of children and adolescents aged 8-18 years referred to Heideheuvel by their own pediatrician. Pediatricians working at Heideheuvel screen the referred participants for eligibility to be included in the treatment. They must have a SDS-BMI ≥ 2.3 according to the growth curves based on the fourth Dutch National Growth Study of 1997 (this corresponds to the 99th percentile) and co-morbidity related to obesity (e.g. obstructive sleep apnea syndrome, raised insulin, diabetes type II, liver function disorders, dyslipidemia, worn out joints) or a SDS-BMI ≥ 3.0 (this corresponds to the 99.9th percentile). Participants will be excluded if they have syndromal or chromosomal determined obesity, obesity caused by endocrine disorders (hypothyroidism, Cushing syndrome, primary hyperinsulinemia, pseudohypoparathyroidism, acquired (structural) hypothalamic damage) or medicine use (e.g. oral steroids, antiepileptic drugs, antidepressants), severe psychiatric problems, an IQ below 75 or similar school level or if their parents are not willing to participate in the treatment. Written informed consents are obtained from both the participants and their parents.

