### Measurements

Primary outcome measure is (SDS) BMI. Secondary outcomes are quality of life and cardiovascular risk factors like blood pressure, bodily circumferences, serum lipids, glucose levels and insulin levels. Eating behavior and physical activity are also assessed. The EuroQoL (EQ-5D) is used to measure quality of life and to calculate Quality Adjusted Life Years (QALYs) over the follow-up period of 24 months. Measurements will be done at four points in time: at baseline (start of treatment) and after 6, 12 and 24 months.

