### Statistical analyses

An intention-to-treat analysis will be performed. A per protocol analysis will also be performed after careful description of correlates of non-adherence and dropout.

To take into account the repeated measurements over time, we will use generalized estimating equations for panel data analysis, also known as cross-sectional time-series analysis, with the use of the Stata software XTGEE command; this will allow us to account for the non-independence of repeated measurements of the same bio-indicator in the same participant over time. Linear regression will be applied for continuous outcomes and logistic regression for dichotomous outcomes. We will use age, sex, time point, and intervention group as explanatory variables in our models.

An economic evaluation from a societal perspective will be conducted alongside the randomized controlled trial. Multiple imputation will be used to impute missing cost and effect data. Five imputed data sets will be created, each of which will be analyzed separately. The results of these five analyses will be pooled using Rubin's rules [27].

Costs generally have a highly skewed distribution. Therefore, bootstrapping with 5000 replications will be used to estimate "approximate bootstrap confidence" (ABC) intervals around cost differences [28,29]. Incremental cost-effectiveness and cost-utility ratios will be calculated by dividing the difference in total costs between the groups by the difference in SDS-BMI and QALYs, respectively. Non-parametric bootstrapping will also be used to estimate the uncertainty surrounding the incremental cost-effectiveness and cost-utility ratios (5000 replications). The bootstrapped cost-effect pairs will be plotted on a cost-effectiveness plane (CE plane) [30] and used to estimate cost-effectiveness acceptability curves (CEA curves). CEA curves show the probability that the intervention is cost-effective in comparison with usual care for a range of ceiling ratios. The ceiling ratio is defined as the amount of money society is willing to pay to gain one unit of effect [31].

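### The listed analysis model leaves out starting SDS-BMI, which is known for every participant; adding it would sharpen the A versus B comparison at no cost

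*Protocol article*

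**What the plan says.** All references are to the protocol article.

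- **Allocation (Design).** The stated method is "A table of random numbers is used to randomize participants". Arm sizes are fixed: 40 adolescents are divided into 10 in A, 10 in B and 20 in usual care (C). A year later, "The participants in group C will be randomized into group A (10) or B (10) after one year of receiving usual care". For the younger age group, "This process is repeated for another 40 participants (8-13 years) after 6 months". The two age bands are therefore drawn separately and arm sizes are controlled. No balancing on SDS-BMI is described.
- **What is known before allocation (Participants; Design).** Eligibility rests on an SDS-BMI threshold, alone or with co-morbidity: "Pediatricians working at Heideheuvel screen the referred participants for eligibility to be included in the treatment". Only then does randomisation follow: "Participants who meet the inclusion criteria and consent to participate in the study will be randomized to one of the three study arms". Under Measurements, SDS-BMI is also measured at the start of treatment and at 6, 12 and 24 months.
- **Outcome (Measurements).** "Primary outcome measure is (SDS) BMI".
- **Model (Statistical analyses).** Generalized estimating equations are used, with these terms: "We will use age, sex, time point, and intervention group as explanatory variables in our models". The same section divides the cost difference by the SDS-BMI difference and bootstraps the ratio. It mentions no baseline adjustment for either.

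**The concern.** Chance will leave the arms somewhat apart on SDS-BMI at the start. Children who start higher tend to stay higher, so part of that gap carries into the follow-up difference. None of the listed terms removes it: there is no baseline covariate, and no group-by-time term is named that would separate a starting difference from a treatment effect.

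Three results are affected: the A versus B difference, each active arm against usual care, and the denominator of the cost-effectiveness ratio. The last may be sensitive, because the Background says that treatment B was developed with the aim of being as effective as A. The true SDS-BMI difference may then be small, and a modest chance gap could change the size or even the sign of the ratio. What is at stake is precision and credibility, not bias.

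**Working it through.** **Inputs from the document.** The main contrast is A versus B with 40 per group (Design; Sample size calculation). In the first year, each active arm has 20 and usual care has 40 over the two age groups. The target difference is 0.5 SDS-BMI, with α = 0.05 and power 0.8.

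**Assumptions, not in the document.** The SD of SDS-BMI is 0.5 at baseline and at follow-up, with a range of 0.4 to 0.6. The correlation r between starting and later SDS-BMI is 0.6 or 0.8. Values are taken as roughly normal. Participants re-randomised from C have the same SD at month 12 as at entry.

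**The plan's own figure.** No SD is given, so 40 per group can be neither confirmed nor refuted. Solving n = 2(1.96 + 0.84)² SD² / 0.5² for n = 40, two-sided, gives SD = 0.80. That is an outcome SD, so for baseline I use it only as an upper scenario.

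**Step 1: size of the chance baseline gap.** SE of the gap = SD × √(1/n₁ + 1/n₂), and P(|gap| > 0.2) = 2[1 − Φ(0.2/SE)]. The 0.2 threshold is my choice; it is 40% of the target difference.

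| SD | A v B, 40 v 40: SE | P(gap > 0.2) | A or B v usual care, 20 v 40: SE | P(gap > 0.2) |
|---|---|---|---|---|
| 0.4 | 0.089 | 3% | 0.110 | 7% |
| 0.5 | 0.112 | 7% | 0.137 | 14% |
| 0.6 | 0.134 | 14% | 0.164 | 22% |
| 0.8 (upper scenario) | 0.179 | 26% | 0.219 | 36% |

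**Step 2: how much of a gap passes through.** With equal SDs, an unadjusted follow-up difference shifts by r × gap. A gap of 0.2 shifts it by 0.6 × 0.2 = 0.12 or 0.8 × 0.2 = 0.16, which is 24% or 32% of the 0.5 target.

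**Step 3: what adjustment gains.** SD of the adjusted A versus B estimate ≈ SE × √(1 − r²). At SD 0.5:
- no adjustment: 0.112
- r = 0.6: 0.112 × 0.80 = 0.089
- r = 0.8: 0.112 × 0.60 = 0.067

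The variance falls by the factor 1 − r², that is by 36% or 64%. This is worth 1/(1 − r²) = 1.56 or 2.78 times the sample size for this contrast.

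**Step 4: would balanced allocation do more?** I simulated the two-cohort design at SD 0.5. One version used simple allocation. The other ranked each batch on SDS-BMI, drew within sets of four (1 A, 1 B, 2 C) and then within pairs for group C. SD of the pooled A versus B estimate:

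| r | Simple, no covariate | Simple, covariate | Matched, covariate |
|---|---|---|---|
| 0.6 | about 0.11 | 0.090 | 0.089 |
| 0.8 | about 0.11 | 0.068 | 0.068 |

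Matching does shrink the baseline gap itself, from an SD of 0.112 to 0.024 for 40 v 40. Once the covariate is in the model, though, the precision of the effect estimate is the same within simulation error.

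**The case against.** The case on the other side has several parts.

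**Random allocation with fixed arm sizes is sound.** This stands. Chance imbalance is part of what the standard error and the 5% error rate already cover. The point is an improvement in precision, not the correction of an invalid method.

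**A reader might infer that the randomisation itself is at fault** because arms of 10 can start well apart. At SD 0.5, a 10 v 10 round has a gap SD of 0.22 and a 37% chance of exceeding 0.2. The document plans no 10 v 10 analysis, however; A versus B is powered and completed at 40 per group. Step 4 also shows that the precision comes from the covariate, not from the allocation.

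**A reader might also infer that each batch was complete and measured before the first draw**, so that ranking would have been straightforward. The text shows that each participant is screened before being randomised. It does not say that all 40 are in hand at once, and the Discussion expects difficult recruitment, especially at ages 8 to 13. Nor does naming a random-number table exclude balancing described in a fuller protocol.

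**It is largely too late to change the allocation.** Data collection began in August 2009, the second cohort was due six months later, and the article mentions software downloaded in July 2010. On that schedule both first-year draws had probably been made. This limits any change to later draws; it does not affect the analysis model.

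**The article might leave baseline adjustment to an analysis plan.** This has some force for the cost-effectiveness analysis, where no covariates are listed either way. It has less for the effect model, whose explanatory variables are named and do not include starting SDS-BMI.

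**Conclusion.** The point holds as one about the analysis model. The listed terms omit a predictor that is already measured and likely to be the strongest one for the primary outcome, so nothing stated corrects a chance starting gap.

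At an assumed SD of 0.5, the chance of an A versus B baseline gap above 0.2 SDS is about 7% (3% to 14% for SD 0.4 to 0.6). Adjustment would lower the SD of that estimate from about 0.11 to between 0.09 and 0.07. Both the SD and the correlations of 0.6 to 0.8 are assumptions. A lower correlation would shrink the gain and a higher one would enlarge it. The documents do not support calling the randomisation defective or the results biased.

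**What to change.** In Statistical analyses:

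1. Add to the model terms SDS-BMI measured before the relevant allocation. For A versus B, this is the screening or baseline value for those allocated directly and the month-12 value for participants re-randomised from group C. For comparisons with usual care in the first year, it is the entry value for everyone.
2. State that the 6, 12 and 24 month values are the outcomes, so that the starting value is a covariate and not also an outcome row.
3. Use the same adjustment for the SDS-BMI difference in the cost-effectiveness ratio, and repeat it within each bootstrap sample.

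Optionally, for any draw still to be made on a complete batch (in particular the re-randomisation of group C), rank participants on SDS-BMI, form pairs, and let the random numbers assign one of each pair to A and one to B. Arm sizes stay 10 and 10. This improves baseline comparability but adds almost no precision beyond item 1.

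The cost is one covariate and a few sentences, settled before the comparative results are seen. No further participants, visits or measurements are needed. Pairing would need only a sorted list before the draw.

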**Figure 1 F1:**
[figure not shown]
**Flow chart of participants**.

### Participants

The study population consists of children and adolescents aged 8-18 years referred to Heideheuvel by their own pediatrician. Pediatricians working at Heideheuvel screen the referred participants for eligibility to be included in the treatment. They must have a SDS-BMI ≥ 2.3 according to the growth curves based on the fourth Dutch National Growth Study of 1997 (this corresponds to the 99th percentile) and co-morbidity related to obesity (e.g. obstructive sleep apnea syndrome, raised insulin, diabetes type II, liver function disorders, dyslipidemia, worn out joints) or a SDS-BMI ≥ 3.0 (this corresponds to the 99.9th percentile). Participants will be excluded if they have syndromal or chromosomal determined obesity, obesity caused by endocrine disorders (hypothyroidism, Cushing syndrome, primary hyperinsulinemia, pseudohypoparathyroidism, acquired (structural) hypothalamic damage) or medicine use (e.g. oral steroids, antiepileptic drugs, antidepressants), severe psychiatric problems, an IQ below 75 or similar school level or if their parents are not willing to participate in the treatment. Written informed consents are obtained from both the participants and their parents.

### Interventions

The intensive combined lifestyle interventions focus on nutrition, physical activity and behavior change of the participants and their parents. Many disciplines are involved, such as pediatricians, dieticians, psychologists, social workers, nurses, physiotherapists, general exercise therapists and exercise therapists Cesar (a specific type of exercise therapy in The Netherlands that is mainly focused on posture, balance and coordination). Additional individual meetings with a psychologist, dietician or social worker are offered if participants, parents or professionals indicate that this is needed. During the inpatient period, children and adolescents will participate in an exercise program four times a week and nutrition education/behavior modification sessions once per week. Behavior modification topics include self-regulation, self-awareness, goal setting, stimulus control, coping skills training, cognitive behavior strategies and contingency management. Behavior modification is achieved through the '5 steps of problem solving'-plan. The first step is to define the problem and learn to describe it. The second step is to search for possible solutions for the defined problem. Step 3 is to make an inventory of the possible consequences for each possible solution described in the second step. The fourth step is to choose the best solution from the possible solutions. The last step then is to implement this solution and to evaluate this afterwards. If the problem is not solved, one can go back to the first step. The nutritional education component of the program will use an approach not primarily aimed at caloric restriction but rather at structured eating and healthier choices, focusing on improving the quality of the dietary intake, and on trying to establish a flexible control of eating behavior. During the weekends at home in the inpatient period the participants and their parents are required to accomplish exercises regarding nutrition and physical activity. During the period when the children are home again the learned behavior is practiced at all times.

Group A will participate in a 6 months intensive inpatient treatment program during weekdays, followed by six monthly return visits of 2 days. Group B will participate in a 2 month intensive inpatient treatment program during weekdays, followed by biweekly return visits of 2 days during the next four months, then followed by six monthly return visits of 2 days. During the inpatient treatment phase and the 2-day return visits all children and adolescents stay overnight at Heideheuvel. Parents of participants in groups A and B will attend 1 session every week during the inpatient period and after that 1 session per return visit of their child. Group C will receive usual care during one year, after which the participants will be randomly allocated to the groups A and B. This implies that during this year they remain under the care of their pediatrician and other health care professionals that might be involved in their treatment like the general practitioner, dietician, physiotherapist and psychologist.

